## 9.2 COVID-19 COHORT STUDY AND NESTED MALARIA TREATMENT TRIAL

### 9.2.1 Pre-Screening (Day 0/1)

Newly diagnosed COVID-19 cases will be eligible for enrolment in the COVID-19 cohort study regardless of malaria status. They will be pre-screened for study eligibility, based on a selection of the inclusion criteria that can be determined without informed consent

#### 9.2.1.1 Pre-screening criteria

1. Confirmed SARS-CoV-2 infection by PCR or antigen test, with positive test results within the past 72 hours
2. Resident in the study area
3. Aged  $\geq 6$  months

If they fulfil the pre-screening criteria, they will be approached for prior consent discussions to determine if they would potentially be willing and able to attend informed consent procedures.

#### 9.2.1.2 Screening and enrolment

If they are potentially interested in joining the study and fulfilling all other inclusion and exclusion criteria the informed consent procedures will be conducted by dedicated staff trained to GCP or equivalent level (see also 2.2.4, Schedule of activities, page 19), the COVID-19 cohort study code issued and the following baseline information collected

- Further demographic information
- Socioeconomic and educational history
- Details of the location of residence
- Tel contact number(s)
- Past and current medical conditions
- Concomitant medication information
- COVID-19 exposure history, including any known exposure to any other, confirmed or suspected COVID-19 cases
- Travel history

A basic physical examination will be performed. Any relevant demographic or health-related information will be copied from existing hospital and clinic records. A venous whole blood sample will be taken (15mL) for further malaria rapid diagnostic test for patient care, and the remaining sample transported within two hours to the laboratories at KEMRI-CGHR in Kisumu and the laboratories of the Groupe de Recherche Action en Santé (GRAS) in Burkina Faso for further processing and storage of whole blood, pellets and serum/plasma (for details, see 2.2.4, Schedule of activities, page 19 and section 10.2, Biological samples, page 45). Some samples will be stored for further distribution to the testing laboratories. In addition, a confirmatory nasal swab will be taken for research purposes and later testing (not for patient care).

Participants will receive a monitoring kit, which will include a digital thermometer and a portable SpO2 pulsometer. They will be instructed on how to self-assess their body temperature, oxygen saturation and respiratory rate in between the scheduled visits (see 9.2.2, Scheduled follow-up visits day 3, 7, 14, 21, 28 and 42, below) and record results daily on a dedicated form. Participants will be instructed that they will be contacted daily by study staff by mobile phone to check on their health status through a brief telephone survey. Participants who don't have a working mobile phone will be issued with a temporary mobile phone from the study, which needs to be returned after study

closeout. Participants will also be instructed how to contact the study team if their symptoms worsen or if they need to contact the research team for other reasons.

### 9.2.1.3 *Nested malaria treatment trial*

Participants with a positive rapid diagnostic test (HRP2 or pLDH band) or positive microscopy for malaria requiring antimalarial treatment will be potentially eligible for enrolment in the nested malaria treatment trial if they provide informed consent and have mild disease and are able to take oral medication (i.e. have uncomplicated malaria). Patients with RDTs that are positive by HRP2 band only will only be followed if subsequent microscopy confirms the presence of asexual parasitaemia.

Participants will be counselled about the preliminary in vitro data on the activity of the planned treatment arms against malaria and SARS-CoV-2 and equipoise regarding efficacy in humans.

They will then be randomised and receive a box or envelop with their study medication. The first dose on day-0 will be provided as directly observed therapy in the clinic.

Participants will be given some clean water for swallowing the tablets. Participants will then be observed for thirty minutes. In the event of vomiting within thirty minutes of administration after the first dose, a repeat dose should be given. If the repeat dose is vomited, the patient should be given the alternative antimalarial drug from the other arm.

If a dose is missed, it should be taken as soon as realised, and then the recommended regimen continued until the full course of treatment has been completed.

The MOH takes malaria RDTs or malaria microscopy at the same time as the COVID-19 swabbing in symptomatic patients only. Asymptomatic patients are not routinely tested for malaria, and this will, therefore, be conducted as part of the screening study on day 0 or if that was not feasible, later when the results of the COVID-19 test become available and patient return for their results on Day-1. Because the malaria test results are typically known within 20 minutes to 2 hours, treatment will need to be initiated that same day. Eligible patients with both a positive SARS-COV-2 antigen test and a positive malaria test on Day-0 will therefore be invited to enrol in the COVID-19 cohort study and the nested malaria treatment trial that same day (Day-0).

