**4. CLINICAL PARTICULARS****4.1 Therapeutic indications**

Pyramax tablets are indicated in the treatment of acute, uncomplicated malaria infection caused by *Plasmodium falciparum* or by *Plasmodium vivax* in adults and children weighing 20 kg or more.

Consideration should be given to official guidance on the appropriate use of antimalarial agents (see section 4.4)

**4.2 Posology and method of administration***Mode of administration*

The dose should be taken orally once a day for three days with or without food.

*Posology**Dosage in adults and children*

Pyramax tablets should be taken orally as a single daily dose for three consecutive days.

| Body weight | Number of tablets | Regimen   |
|--------------------|--------------------------|------------------|
| 20 - < 24 kg       | 1 tablet                 | Daily for 3 days |
| 24 - < 45 kg       | 2 tablets                | Daily for 3 days |
| 45 - < 65 kg       | 3 tablets                | Daily for 3 days |
| ≥ 65 kg            | 4 tablets                | Daily for 3 days |

A granule formulation is available for children weighing between 5 kg to under 20 kg.

In the event of vomiting within 30 minutes of administration after the first dose, a repeat dose should be given. If the repeat dose is vomited, the patient should be given an alternative antimalarial drug. In the event of non-severe diarrhoea normal dosing should be continued.

If a dose is missed, it should be taken as soon as realised and then the recommended regimen continued until the full course of treatment has been completed.

*Dosage in paediatrics population*

Pyramax is dosed according to body weight. The safety and efficacy of Pyramax tablets has not been established in children below 20 kg body weight. The clinical studies conducted in *Plasmodium vivax* malaria, included only 13 patients below 12 years old (see section 5.1.)

*Elderly*

Clinical studies did not include patients aged 65 years and over. No dosing adjustments are necessary based on present knowledge and the short 3 day course of treatment. However, considering the possibility of age-associated decrease in hepatic and renal function, caution should be exercised when administering the product to the elderly.

*Dosage in hepatic and renal impairment*

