### 16.7.2 Artemether-lumefantrine

On the next pages, an example is given of a Summary of the product characteristics for Coartem® from Novartis, which is approved by a stringent regulator. Other WHO pre-qualified brands, such as Lumartem from CIPLA may also be used.

Source of the summary of product characteristics for RiaMet/Coartem®:

<https://extranet.who.int/prequal/sites/default/files/documents/MA069part4v1.pdf>

Artemether 20mg/lumefantrine 120mg  
Dispersible tablets (Novartis Pharma AG), MA069

WHOPAR part 4

12/2011

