## 4. CLINICAL PARTICULARS

### 4.1 Therapeutic indications

This medicinal product is for pediatric use only.

Riamet Dispersible/ Coartem Dispersible is indicated for the treatment of children and infants with acute, uncomplicated infections due to *Plasmodium falciparum* or mixed infections including *P. falciparum*. Riamet Dispersible/ Coartem Dispersible may be used for self-administration, as stand-by emergency treatment in cases of suspected malarial infection, when no doctor can be reached within 24 hours or the medicinal product is not locally available.

Riamet Dispersible/ Coartem Dispersible is effective against both drug-sensitive and drug-resistant *P. falciparum*, and it is therefore also recommended for malaria infections acquired in areas where the parasites may be resistant to other antimalarials.

Consideration should be given to official guidelines and to local recommendations based on the prevalence of resistance to antimalarial agents. Official guidelines are those issued by the WHO and by health authorities.

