### 4.2 Posology and method of administration

Riamet Dispersible/ Coartem Dispersible is not recommended for use in children below 5 kg body weight due to a lack of data on safety and efficacy.

Dispersible tablets for oral administration. The dispersible tablet(s) for one dose should be stirred in a small amount of water (approximately 10 ml per tablet) so that the active substance can be better dispersed before the suspension is drunk. Stir gently and administer immediately to the patient. Pour some more water (approximately 10 ml) into the glass and give immediately to the patient.

Artemether 20mg/lumefantrine 120mg  
Dispersible tablets (Novartis Pharma AG), MA069

WHOPAR part 4

12/2011

Food or drinks (such as milk) that are rich in fat should be consumed following ingestion of the dose even though patients with acute malaria are frequently averse to food. Patients should be encouraged to resume normal eating as soon as possible, since this improves absorption of artemether and lumefantrine.

In the event of vomiting within one hour of administration, a repeat dose should be taken. The dispersible tablet is indicated only for infants and children. A separate tablet formulation is available for adolescents and adults.

Treatment should be administered at the time of initial diagnosis or at the onset of symptoms.

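### For children of 5 to <15 kg on artemether-lumefantrine, the common vomiting rule in section 9.2.1.3 is shorter and narrower than the artemether-lumefantrine label that the protocol appends

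*Protocol*

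**What the plan says.** Protocol section 9.2.1.3 describes the directly observed first dose. Observation is short: "Participants will then be observed for thirty minutes". The re-dosing rule is: "In the event of vomiting within thirty minutes of administration after the first dose, a repeat dose should be given". It continues: "If the repeat dose is vomited, the patient should be given the alternative antimalarial drug from the other arm". No arm is named, and the reference to the other arm makes sense only if the rule covers both AL and PA.

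Appendix VII reproduces the product texts.

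- PA (16.7.1, section 4.2 of the tablet label): "In the event of vomiting within 30 minutes of administration after the first dose, a repeat dose should be given". The granules label says the same.
- AL (16.7.2, section 4.2): "In the event of vomiting within one hour of administration, a repeat dose should be taken". No restriction to the first dose is stated.

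The AL text has limited standing. It is introduced with the words "an example is given of a Summary of the product characteristics for Coartem® from Novartis", and other prequalified brands may be used. It also covers one formulation: "This medicinal product is for pediatric use only", and "A separate tablet formulation is available for adolescents and adults". Table 1 (section 7.1.2) gives AL dispersible tablets at 5 to <15 kg and standard 40/240 mg tablets from 15 kg.

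Two other places touch on re-dosing. Section 10.10.2 allows study drug to be given again after vomiting, without naming a window, dose or arm. Section 7 refers dosing to WHO guidelines, which are not reproduced.

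**The concern.** The common rule follows the PA label and is applied to a drug whose appended label says something else. In the affected weight band the PA arm is handled as its label directs and the AL arm is not.

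What is at stake is first a matter of care. A small child on AL could lose a dose 45 minutes after taking it, when observation has ended, and the section that governs dosing would not call for a replacement. The AL label (section 5.2) says that lumefantrine absorption begins after a lag of up to 2 hours and that artemether peaks at about 2 hours. Much of such a dose may therefore be lost. That is an inference; the label does not give it as the reason for its window.

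Second, any resulting malaria failure would fall in the AL arm and enter the secondary comparison of antimalarial efficacy to day 42 (section 4.3).

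**Working it through.** No figure in the protocol bears on this, so the check is a comparison of texts.

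| | Trial rule, 9.2.1.3 | PA labels, 16.7.1 | AL dispersible label, 16.7.2 |
|---|---|---|---|
| Re-dosing window | 30 min | 30 min | 60 min |
| Doses covered | first | first | any of the 6 |
| If the repeat is vomited | drug of the other arm | an alternative antimalarial | not stated |

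1. **Source of the rule.** The trial rule agrees with both PA labels on window and on dose, and almost in wording. It agrees with the AL label on neither.
2. **Gap for AL.** After the first dose, 60 - 30 = 30 minutes are not covered. Doses 2 to 6 have no window at all. Section 7.4.2.3 places these later doses at home or on the ward.
3. **Who is directly affected.** At 5 to <15 kg, AL children receive dispersible tablets and PA children receive granules (Table 1). Both labels are in the appendix, so at the same body weights the two labels differ and the protocol follows only one.
4. **Who is not shown to be affected.** From 15 kg, AL patients take standard tablets. Their label is not in the protocol, so whether it also says one hour is unknown from the documents.
5. **Does other text close the gap?** Section 10.10.2 permits re-dosing but sets no window, and section 7 points to guidelines that cannot be read here. Neither forbids re-dosing and neither supplies the AL instruction. The dosing-instructions row of Table 1 is blank in the text available, so it cannot be said whether it carried arm-specific advice.
6. **Size.** With 1:1 allocation, 142/2 = 71 patients are expected on AL, so one extra failure shifts the AL proportion by 1/71 = 1.4 percentage points. Going further would need the number of AL children of 5 to <15 kg, the timing of vomiting after AL, and the chance that a missed replacement leads to failure. The protocol gives none of these.

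**The case against.** The best case for leaving the rule alone is that the AL label is not the trial's dosing standard. It is an example, for one paediatric formulation, and WHO guidelines govern dosing. This stands for patients of 15 kg or more. It is weaker below 15 kg, where the trial uses the formulation that the label describes.

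There are also safeguards. Section 10.10.2 leaves a clinician free to re-dose, participants are telephoned daily between visits about adherence and symptoms, treatment response is assessed to day 42, and malaria recurring from day 7 is re-treated (9.2.7). These make harm less likely, but they depend on someone acting without an instruction.

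One common rule also has a merit in an open-label trial: observing the arms for different times would make staff detect early adverse events differently by arm. That is a sound objection to lengthening observation for AL alone, and the fix below takes it into account.

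Three stronger readings are tempting and are not supported.

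- A reader might infer that the whole AL arm is dosed against its label. No label for the standard tablets is shown.
- A reader might take the 17.5% vomiting rate in the AL label (section 4.8), multiply by 71, and report about 12 affected patients. That rate is for vomiting at any time. The label attributes most such events to malaria or an inadequate response to treatment rather than to the drug. The product is paediatric, while the trial enrols all ages from 6 months. No share falling between 30 and 60 minutes can be derived.
- A reader might infer that the efficacy comparison is biased against AL. The direction is plausible, but a failure requires vomiting in the gap, no one re-dosing, and one lost dose of six proving decisive.

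**Conclusion.** The rule in 9.2.1.3 conflicts with the appended AL dispersible-tablet label, in both the window and the doses covered, for AL children of 5 to <15 kg. For heavier AL patients it is a point to check and not an established error. The conclusion assumes that the appended label represents the dispersible product actually used, since another prequalified brand could differ.

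The number of children affected and the effect on the day-42 malaria comparison cannot be derived and are likely small. That comparison is one of several secondary endpoints in a trial described as exploratory. The primary endpoint, SARS-CoV-2 clearance at day 7, is not affected: the PA arm follows its own label, and section 3.2.3 credits lumefantrine with no antiviral activity in vitro. The reason to act is patient care at low cost.

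**What to change.** In section 9.2.1.3:

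- Set the AL re-dosing window to one hour for dispersible tablets, for any dose. Extend it to standard tablets if their label or the WHO guideline agrees.
- Keep the 30-minute re-dosing window for PA.
- Observe both arms for one hour after the first dose, so that early adverse events are looked for equally.

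In section 7.4.2.3, apply the AL window to ward doses, and tell participants to telephone the study team if a home dose is vomited within it. A replacement must then be supplied, because study drug is pre-packed per participant (section 7.3).

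Cost: an amendment with ethics approval, a short site instruction, and a small stock of replacement doses. Extra observation is at most 142 x 0.5 h = 71 patient-hours over the trial. It brings some added contact with infectious patients, against the aim stated at the start of section 9 of keeping contact low. Waiting in the separate ventilated areas of section 12.7.3.1 would limit this. A wider window may lead to a few more repeat doses and, if a repeat is also vomited, an occasional extra switch to PA. No extra visits, samples or participants are needed.

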### 9.2.2 *Scheduled follow-up visits day 3, 7, 14, 21, 28 and 42*

We will follow local MoH guidelines in each country to determine if a participant requires hospitalisation and for how long, or if a participant will be invited to self-isolate at home.

Participants who are self-isolating will be asked to return to the study clinics for scheduled follow-up visits on days 3, 7, 14, 21, 28 and 42. Of these visits, the follow-up visits on day 21 and 42 apply to the participants enrolled in the nested malaria treatment trial only. During each of these scheduled follow-up visits, a similar symptom questionnaire will be filled out, concomitant medication will be reviewed, and brief physical examination performed, and the respiratory rate and pulse, body temperature and O2 saturation taken by study staff. The participant will be asked to bring the form with the self-assessed values for body temperature and O2 saturation values that were taken by the participant at home for verification of the data and the technique used by the participant. A photo will be taken of the self-assessment form for subsequent data entry and verification. Where relevant, any relevant demographic or health-related information will again be copied from existing hospital and clinic records. Similar venous blood samples (ml), swab samples will be taken as on enrolment.

Participants who will be admitted on isolation wards will be monitored daily for signs and symptoms of severe COVID-19, and have daily respiratory rate, body temperature and O2 saturation measured. Similar blood and swab samples will be taken for participants who are self-isolating.

If participants are enrolled in the nested malaria treatment trial will have an additional 5mL of whole blood taken for antimalarial drug levels from the same blood draw as the overall sample (i.e. the total blood volume per blood draw on days 3, 7, 14, 21, 28 and 42 will be 20mL (15mL for the above-mentioned assays under 'k' in the section 2.2.4, Schedule of activities page 19 and 5mL for pharmacokinetics). The volume samples in children below the age of assent will be less and based on bodyweight (total 2.5 mL <10kg and 5 mL 10-<15kg per sample) (see section 12.7.1.4, Maximum blood volume, page 63) and will be excluded from the pharmacokinetic sampling.

The data collected on these days will also be used for the assessment of the antimalarial treatment response as described in section 10.3.2, Assessment of the antimalarial treatment response, page 47.

